#### PTSD risk factors

Table 2 summarizes the biopsychosocial factors that have the potential to increase PTSD occurrence. These factors will be assessed at inclusion in the ED. Estimated time for documenting all the questionnaires is around 30 min.

**Table 2 Tab2:** PTSD risk factors evaluated in the study, evaluation instruments and timing

Factor Category	Predictive Factors	Measure	Timeline
Trauma Characteristics	Type and timing of the trauma	Pre-screening questionnaire	1st visit
	After trauma: Hospitalization (±); Intensive care (±)	Consumer file	1st visit
Demographics	Sex	Consumer file	1st visit
	Age	Consumer file	1st visit
	Socio-economic status	Self-administered questionnaire	1st visit
	Educational level	Self-administered questionnaire	1st visit
	Marital status	Self-administered questionnaire	1st visit
Biological	Heart rate	Consumer file	1st visit
	Blood pressure	Consumer file	1st visit
	Blood alcohol level	Consumer file	1st visit
Psychological	Trauma history	Self-administered questionnaire	1st visit
	Chronic anxiety	STAI-Y (A & B forms) [68, 69]	1st & Final visits
	Past and current psychiatric pathology	Self-administered questionnaire	1st visit
	Current psychotropic treatment at inclusion and during the 3-month period	Self-administered questionnaire	1st & Final visits
	Psychological care during the 3 months	Self-administered questionnaire	Final visit
	Dissociative Experiences	Self-administered questionnaire: PDEQ [70]	1st visit
Social	Alcohol misuse	Self-report: AUDIT [73, 75]	1st & Final visits
	Smoking addiction	Self-administered questionnaire: Fagerström test [74]	1st & Final visits
	Family history of psychopathy or instability	Self-administered questionnaire	1st visit
	Marital stability	Self-administered questionnaire	1st visit
	Social support	Self-administered questionnaire: SSQ6 [71, 72]	1st & Final visits
Others	Somatic pathology	Patient file	1st visit
	Emergency care time	Patient file	1st visit

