## Abstract

**Background:**

Traumatic exposure is a frequent issue in patients visiting emergency departments (EDs). Some patients will subsequently develop post-traumatic stress disorder (PTSD) while other will not. The problem is under-diagnosed in EDs and no standardized management is provided to prevent PTSD. Most studies focused on a particular group of trauma whereas we need a global approach to further develop interventions for detecting and treating patients at high risk. We aim to assess the prevalence of traumatic exposure and situation at high risk of further PTSD and identify pre and peri-traumatic biopsychosocial factors predisposing individuals to PTSD in the general context of EDs.

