At inclusion, we will evaluate patient’s social support as a risk factor and at 3-month follow-up as a psychosocial and occupational consequence of the trauma. For this purpose, we will ask his/her return time to the workplace and use the validated French version of the Social Support Questionnaire 6 (SSQ6) [71, 72]. SSQ6 is a 6-item questionnaire that measures two aspects of perceived social support, i.e. availability and satisfaction. Availability is defined as the individual’s estimation of the number of people who can help him/her if required. Satisfaction is defined as the perceived adequacy between the support received and his/her expectations and needs. For each item, the respondent lists the people (max. 9) he/she can count on in the situation described and expresses his/her degree of satisfaction (from 1 to 6) with regard to this support. We then calculate one score for availability (score N, that varies from 0 to 54), and another for satisfaction (score S, that varies from 6 to 36).

For the assessment of alcoholism and nicotine dependence at inclusion and at 3-month follow-up (as PTSD-related complications), we will use Alcohol Use Disorder Identification Test (AUDIT) and Fagerström test, respectively [73, 74].

The AUDIT consists of 10 questions and screens for risky or harmful use of alcohol. It is the reference for detecting alcohol misuse. Men scoring ≥7 and women scoring ≥6 raise the suspicion of alcohol misuse [73, 75].

The Fagerström test is a quick 6-item test that quantifies patient’s level of nicotine dependence [75]. The score ranges from 0 to 10. Dependency is deemed to be null if the score is from 0 to 2, low from 3 to 4, average from 5 to 6, strong from 7 to 8, and very strong from 9 to 10.

In order to assess depression and suicidal ideation (as risk factors at inclusion), and as PTSD-related complications or comorbidities at 3 months, we will use the Quick Inventory of Depressive Symptomatology (Self-Report) (QIDS-SR16). The QIDS-SR16 is a self-administered questionnaire with 16 items describing the 9 symptom domains of DSM-IV associated with depressive feeling [76–78]. The assessment of depression severity is based on the total score as follows: from 1 to 5, absence of depression; from 6 to 10, slight depression; from 11 to 15, moderate depression; from 16 to 20, severe depression; and from 21 to 27, very severe depression. We will also ask for the number of suicide attempts over the last 3 months.

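### Table 2 lists psychological care and psychotropic treatment during follow-up as predictive factors, although the factors are said to be assessed at inclusion, and the model description does not exclude them

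*Protocol article*

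**What the plan says.** The abstract sets the aim: to "identify pre and peri-traumatic biopsychosocial factors predisposing individuals to PTSD in the general context of EDs". The section on PTSD risk factors opens with "Table 2 summarizes the biopsychosocial factors that have the potential to increase PTSD occurrence" and continues with "These factors will be assessed at inclusion in the ED".

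Table 2 follows, with one column for predictive factors and one for timeline. Two of its rows do not fit that introduction:

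- "Psychological care during the 3 months", with a timeline of the final visit only.
- "Current psychotropic treatment at inclusion and during the 3-month period", with a timeline of first and final visits.

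The section on primary outcome criteria analysis estimates crude and adjusted odds ratios for the studied factors by univariate and multivariate logistic regression, with at most twelve explanatory variables in the multivariate model. It names no candidate variables and does not limit them to values recorded at the first visit. Table 2 is the only consolidated list of factors in the article.

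**The concern.** A value that comes into being between inclusion and month 3 is neither pre- nor peri-traumatic, and it does not exist when a patient is seen in the ED. The background section gives early identification of high-risk patients as the reason for studying predictors, and a variable known only at month 3 cannot serve that purpose.

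There is also a risk of bias. Under the data collection section, care received over the 3 months is established at the same telephone interview as the PCL-5. Patients may seek or receive care because symptoms are developing, so an association between care and PTSD can run from outcome to supposed predictor. Care may also follow baseline severity. The crude odds ratio would then mix reverse causation, confounding by severity and any true benefit of care. In the multivariate model, adjusting for care would condition on something downstream of acute stress at inclusion, which can distort the odds ratios of the baseline factors that the cohort is meant to estimate.

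**Working it through.** **1. The plan's own figure.** The sample size section assumes 40% PTSD in the unexposed, a relative risk of 1.4, alpha 0.05 and 80% power, and arrives at 305 patients. The exposed risk is 1.4 × 0.40 = 0.56. Assuming a two-sided test, a 1:1 exposure split and no continuity correction (none of these is stated), with mean proportion 0.48:

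n per group = [1.96 × √(2 × 0.48 × 0.52) + 0.842 × √(0.40 × 0.60 + 0.56 × 0.44)]² / 0.16² ≈ 152, or 304 in total.

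The stated 305 is reproduced to within one patient. The point made here concerns variable timing and does not alter this number.

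**2. The target effect as an odds ratio.** The models report odds ratios, so the relative risk of 1.4 is converted:

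(0.56 / 0.44) / (0.40 / 0.60) = 1.273 / 0.667 = 1.91.

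**3. Timing of the Table 2 rows.** Of 23 rows, 6 carry a final-visit timing:

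| Row | Timeline | Role of the 3-month value elsewhere in the article |
|---|---|---|
| Psychological care | Final only | None assigned; Table 1 only schedules its collection |
| Psychotropic treatment | First and final | None assigned; Table 1 only schedules its collection |
| STAI-Y | First and final | Impact of the trauma (data collection) |
| SSQ6 | First and final | Impact or consequence (data collection; secondary outcome criteria) |
| AUDIT | First and final | PTSD-related complication (secondary outcome criteria) |
| Fagerström | First and final | PTSD-related complication (secondary outcome criteria) |

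Only the first two rows have a follow-up value that the article calls a predictive factor and gives no other analytic role.

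**4. Illustration of reverse causation.** The article gives no care uptake, so these rates are assumptions. Care is taken to have no effect on PTSD, and 20% of patients without PTSD receive it. With uptake p among those with PTSD:

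OR = [p / (1 − p)] / (0.20 / 0.80) = [p / (1 − p)] / 0.25.

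| Uptake with PTSD | Uptake without PTSD | OR for care |
|---|---|---|
| 20% | 20% | 0.250 / 0.25 = 1.0 |
| 30% | 20% | 0.429 / 0.25 = 1.7 |
| 40% | 20% | 0.667 / 0.25 = 2.7 |
| 50% | 20% | 1.000 / 0.25 = 4.0 |

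The odds ratio reaches 1.91 when p / (1 − p) = 1.91 × 0.25 = 0.477, that is p = 0.477 / 1.477 ≈ 32%. On these assumptions, uptake of about 32% against 20% would produce an odds ratio as large as the design's target without any causal effect of care.

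**The case against.** **Nothing says these values will be modelled.** The analysis section refers only to the studied factors, the cap of twelve rules out entering all 23 rows together, and a candidate list is commonly left to the full protocol or analysis plan. The timing sentence and the stated aim both point towards baseline values. This stands in part. A reader might infer that reverse causation will enter the model, but the article supports only that it is not excluded. It does not clear the two rows, because the contradiction lies within the section itself: a final-visit-only item is called a predictive factor assessed at inclusion.

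**The other repeated measures.** A reader might infer that 3-month anxiety, alcohol use, smoking and social support are also offered as predictors, because their rows carry both visits. The documents do not support this. The secondary outcome criteria treat "social support as a risk factor and at 3-month follow-up as a psychosocial and occupational consequence of the trauma" and describe "alcoholism and nicotine dependence at inclusion and at 3-month follow-up (as PTSD-related complications". The data collection section treats 3-month STAI-Y and SSQ6 as trauma impact, and the secondary analysis sections report the 3-month scores as outcomes. For these rows the timeline column reads as a measurement schedule.

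**The odds ratios are assumed.** This stands. A reader might infer that spurious factors would outrank real ones, but the lowest scenario gives 1.0, the next gives 1.7 (below 1.91), and 1.91 is the smallest effect the design aims to detect rather than the expected effect of a true predictor. A real benefit of care would also pull the odds ratio down.

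**Care steered by severity.** Patients with an IES-R above 34 are to be offered a specialist consultation, but the article does not say when. The offer is compatible with confounding by severity and does not establish it.

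**Adjustment for treatment can be legitimate.** It can, in an analysis labelled as such. The article instead lists care among the predictive factors.

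**Conclusion.** The point holds for two rows of Table 2: psychological care during the 3 months, and the follow-up part of psychotropic treatment. Both contradict the table's own timing sentence and the pre- and peri-traumatic aim. Because the primary analysis does not limit candidates to first-visit values, they could be modelled as predictors of an outcome they may partly result from.

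Under assumed uptake of 20% without PTSD and 20% to 50% with PTSD, and no effect of care, the resulting odds ratio lies between 1.0 and 4.0, against a design value of about 1.9. The range shows that the bias could be as large as the effects sought; it is not a forecast. Sample size and data collection are unaffected. The matter should be corrected because it bears on the primary objective of the cohort and is easily put right.

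**What to change.** - In the section on primary outcome criteria analysis, add one sentence: candidate predictors for the primary univariate and multivariate models are values recorded at the first visit only.
- In Table 2, remove psychological care during the 3 months from the predictive factors, and limit the psychotropic row to treatment at inclusion.
- Report psychological care and psychotropic treatment during follow-up descriptively, for example by 3-month PTSD status and baseline IES-R level, or in a separately labelled secondary analysis.

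The cost is one table edit and one sentence, with no change to the data collected or the number of patients. The small downside is that the primary model no longer accounts for intercurrent care, so its odds ratios describe prediction under whatever care patients happened to receive. The separate analysis can address that.

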### Sample size

The total number of ED visits in the assigned six centers over a period of 1 month is more than 20,000. We plan to screen around 15,000 patients (75%) with an age range of 18 to 70. Following a traumatic context, 10 to 50% of survivors consult EDs [3, 15, 79, 80]. Considering the most conservative hypothesis (10% of the 15,000 visiting 18–70 year old patients), we estimate that 1500 patients could be included in the study to participate in the cross-sectional part of the study.

The main objective of the cohort study is to identify factors associated with the occurrence of 3-month PTSD. In the literature, incidence of PTSD in various populations and after different types of trauma usually ranges from 30 to 60% [3, 15, 79, 80]. Considering the hypothesis of a 40% incidence of PTSD in the “unexposed” group, the inclusion of 305 patients should allow, with an alpha risk of 0.05, and a power of 80%, to identify factors associated with a relative risk of at least 1.4 [81].

As we anticipate 30% of the subjects may be either lost to follow-up or unwilling to participate at 3 months, we will randomly select a cohort of 400 patients.

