## Background

Post-traumatic stress disorder (PTSD), one of the most serious sequelae of a traumatic exposure, is a chronic disorder with a high level of anxiety and neurovegetative symptoms that interrupt normal psychosocial functioning of the person [1–4]. There are four main categories of diagnostic symptoms, namely, symptoms of re-experiencing the trauma, avoidance and numbing symptoms, negative alterations in mood and cognition, and hyper-arousal symptoms. [4–9]. The mean duration of PTSD is 5.3 years (range: 0.2–28.1) [10]. Patients with PTSD are more likely to develop other psychiatric disorders such as depression, anxiety disorders, substance use disorders, and/or attempt suicide [11, 12]. The likelihood of developing somatic pathologies such as cardio-vascular disorders is also very high [13, 14]. Therefore, such patients, in addition to the disorder itself, suffer from its physical, occupational, and social sequelae. Such consequences result in a significant economic impact [5].

Worldwide approximately 60.7% of all men and 51.2% of all women encounter at least one traumatic event in their lifetime. However, not all of them will develop PTSD; it is estimated that after a trauma, 8% of men and 20% of women will subsequently develop PTSD [15]. Prevalence of the condition is highly variable (4–86%), but is higher among those who experienced the stressors directly, such as victims of intimate partner violence (IPV), sexual victimization, servicemen, refugees, and asylum seekers [5]. In the French population, the lifetime exposure to a traumatic event is estimated to be 72.7% and lifetime prevalence of PTSD to 3.9% [10], which is lower than that found in the United States (7.8%), but higher than rates in Spain (2.2%) or Italy (2.4%) [10].

Among the patients consulting EDs after a recent trauma, 18 to 42% suffer from acute stress disorder (ASD) [16–18], which is highly predictive of subsequent occurrence of PTSD [16, 19, 20]. However, ASD is often underdiagnosed in ED, mainly due to the assessment focused on urgent physical problems, complaints of the patient (pain, insomnia), and overlooking the traumatic context [1, 21].

PTSD predictive factors are worthwhile for identifying populations at high risk, which in turn could lead to early diagnosis and management of these cases, and therefore could help reduce the occurrence of the disorder. Screening for such factors, however, is not incorporated into any structured assessment procedure in EDs.

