#### Primary outcome criteria analysis

To assess the baseline risk of developing PTSD based on the IES-R score (< 12, 12 to 34, > 34) we will calculate the proportion of the subjects at high risk (IES-R score > 34) and moderate-risk (IES-R score 12 to 34) to develop PTSD and their 95% confidence interval.

To analyze the biopsychosocial factors associated with the occurrence of PTSD at 3 months (yes / no) we will employ a univariate model. For statistical testing, we will use the Chi-squared test for qualitative variables, Student’s test for quantitative variables following a normal distribution, Wilcoxon test for quantitative variables following a non-normal distribution, and a Kruskal & Wallis rank test for ordered quantitative variables of the score type. Univariate and multivariate logistic regression modeling will facilitate estimation of the association between the studied factors and the 3-month risk of PTSD by calculating the crude and adjusted odds ratio and their 95% confidence interval.

Among 305 analyzable patients, with a 40% incidence rate of PTSD, we expect 122 patients in the PTSD group. To ensure the convergence and robustness of the statistical model, we will not integrate more than twelve explanatory variables into the multivariate predictive model [82].

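### The 80% power for a relative risk of 1.4 assumes an unstated even exposure split, and 40% PTSD is used once as the unexposed rate and once as the overall rate

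*Protocol article*

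**What the plan says.** In the protocol article, Sample size, the cohort is sized on a comparison of exposed with unexposed patients: "Considering the hypothesis of a 40% incidence of PTSD in the “unexposed” group", "the inclusion of 305 patients should allow", with alpha 0.05 and 80% power, "to identify factors associated with a relative risk of at least 1.4". No exposure frequency and no ratio of exposed to unexposed is given. The same section cites a literature range for PTSD incidence of 30 to 60%.

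Under Statistical methods, Primary outcome criteria analysis, the 40% returns with a different denominator: "Among 305 analyzable patients, with a 40% incidence rate of PTSD, we expect 122 patients in the PTSD group". That count leads to the limit on model size: "we will not integrate more than twelve explanatory variables into the multivariate predictive model".

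Table 2 lists the candidate predictors. Some are binary, such as hospitalisation and intensive care. Many are continuous or scores, such as age, heart rate and the questionnaire totals. No frequencies are given.

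**The concern.** Finding predictors of 3-month PTSD is the primary objective of the cohort, so the power statement is what tells a reader which associations the study could have missed. It speaks of factors in general, yet the power of a two-group comparison depends on how the patients divide between the groups. If the calculation assumed an even split, the stated power does not carry over to uncommon factors, and a null result for one of them would look better supported than it is.

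The two uses of 40% raise a related question. If a factor raises risk by a relative 1.4, the overall incidence must lie above the incidence in the unexposed. The same number cannot be both, and the choice changes both the power and the expected number of cases.

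**Working it through.** **Inputs.** From Sample size: alpha 0.05, power 80%, p0 = 0.40 in the unexposed, relative risk 1.4, N = 305. Hence p1 = 1.4 × 0.40 = 0.56. Sidedness is not stated; I take two-sided. The exposed fraction f is not stated and is varied below.

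**Step 1: reproduce 305.** Pooled-variance formula for two proportions, equal groups, mean rate p̄ = (0.40 + 0.56)/2 = 0.48:

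n per group = [1.96 √(2p̄(1−p̄)) + 0.8416 √(p0(1−p0) + p1(1−p1))]² / (p1 − p0)²
= (1.3848 + 0.5870)² / 0.16² = 151.9

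This rounds to 152 per group, 304 in total, against the stated 305. Other even-split formulas come close: arcsine 304, unpooled 299, log odds ratio 309, log relative risk 317. A one-sided test gives 240. So 305 corresponds to a two-sided test and an even split.

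**Step 2: power at N = 305 for other exposure frequencies.** With n1 = 305f, n0 = 305(1−f) and p̄ = f·p1 + (1−f)·p0:

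power = Φ{[(p1 − p0) − 1.96·s0] / s1}, where s0 = √[p̄(1−p̄)(1/n0 + 1/n1)] and s1 = √[p0(1−p0)/n0 + p1(1−p1)/n1].

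For f = 0.5: (0.16 − 1.96 × 0.0572)/0.0565 = 0.85, power 80.2%. For f = 0.2 (61 exposed, 244 unexposed): (0.16 − 1.96 × 0.0709)/0.0709 = 0.30, power 61.7%.

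| Exposed (assumed) | Power for RR 1.4 | RR detectable with 80% power | N needed for RR 1.4 |
|---|---|---|---|
| 60% | 78.5% | 1.41 | 318 |
| 50% | 80.2% | 1.40 | 304 |
| 40% | 78.6% | 1.41 | 317 |
| 30% | 73.2% | 1.43 | 360 |
| 20% | 61.7% | 1.50 | 472 |
| 10% | 39.8% | 1.65 | 832 |

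**Step 3: the two meanings of 40%.**

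- As the unexposed rate, at an even split and RR 1.4: overall incidence is 0.5 × 0.40 + 0.5 × 0.56 = 48%, and 305 × 0.48 = 146 cases. The analysis section expects 305 × 0.40 = 122.
- As the overall rate, at an even split and RR 1.4: p0 = 0.40/(1 + 0.4 × 0.5) = 33.3% and p1 = 46.7%. Power is Φ[(0.1333 − 1.96 × 0.0561)/0.0556] = Φ(0.42) = 66.3%. Reaching 80% needs 211 per group, 422 in total.

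**Step 4: the article's own incidence range, at an even split and N = 305.**

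- 30% in the unexposed (30% vs 42%): power 58.9%, detectable RR 1.52.
- 50% in the unexposed (50% vs 70%): power 94.9%, detectable RR 1.32.

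**Step 5: the limit of twelve variables.** 122/12 = 10.2 cases per variable. Under the sample-size inputs with 10% to 50% exposed, overall incidence runs from 41.6% to 48%, which is 127 to 146 cases. The 122 is therefore slightly conservative under those inputs. At 30% overall incidence there would be 305 × 0.30 = 91.5 cases, and the same ratio of about ten allows nine variables.

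**The case against.** The strongest defence is that 305 is correct under the conventional even split, and that an article condensing a protocol may leave the split to the full document. The first half stands: there is no arithmetical error in 305. The second half does not fully answer the point. The article makes a general claim about factors with a relative risk of 1.4 or more, and as worded that claim does not hold for uncommon factors. The two denominators for 40% also stand in the article itself.

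Four stronger readings are tempting, and the documents do not support them.

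- *The claim fails away from exactly 50% exposure.* Power is still about 79% at 40% or 60% exposure. With 50% PTSD in the unexposed it is 81.6% even at 20% exposure.
- *The design is underpowered for most of its factors.* The article gives no factor frequencies, and many Table 2 factors are continuous or scores that a binary-exposure calculation does not describe.
- *The expected incidence is really 8 to 20%.* The Background does say that "8% of men and 20% of women will subsequently develop PTSD", but of trauma in general. The Objectives describe a cohort at moderate or high risk, and Sample size cites 30 to 60%. The Background figures cannot be carried over as the cohort's rate.
- *Twelve variables is too many.* The text sets a maximum, so fewer may be used, and Step 5 shows it is conservative under the sample-size inputs.

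It is also fair to say that the planned odds ratios with 95% confidence intervals will show directly what a null result excludes. That limits the harm, but it does not correct the power statement.

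**Conclusion.** The point holds in a limited form. The 80% power applies to a binary factor present in about half the patients with 40% PTSD in the unexposed, and the article leaves out the first of these conditions. Power for RR 1.4 is 73% at 30% exposure, 62% at 20% and 40% at 10%. Separately, the 40% in Sample size and the 40% in Primary outcome criteria analysis cannot both hold for a factor with the planned effect. At an even split the gap is 48% against 40% overall, or 146 against 122 cases. Reading 40% as the overall rate lowers power to 66%. The gap narrows for rarer factors (41.6% overall at 10% exposure). Over part of the cited incidence range the even-split result moves from 59% power (30% in the unexposed) to 95% (50%), so the uncertainty runs both ways.

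These figures rest on assumed exposure frequencies, a two-sided test, the pooled-variance formula, and an unadjusted comparison. Adjustment for correlated factors would usually lower power further.

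**What to change.** 1. In Sample size, restate the claim: 305 analysable patients give 80% power, two-sided alpha 0.05, for a relative risk of 1.4 for a binary factor present in about 50% of patients, with 40% PTSD incidence in the unexposed.
2. Add a small table of relative risks detectable with 80% power at N = 305, for exposure of 10, 20, 30 and 50% across the cited incidence range. By the formula in Step 2:

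| PTSD in unexposed | 10% exposed | 20% | 30% | 50% |
|---|---|---|---|---|
| 30% | 1.85 | 1.64 | 1.56 | 1.52 |
| 40% | 1.65 | 1.50 | 1.43 | 1.40 |
| 50% | 1.51 | 1.39 | 1.34 | 1.32 |
| 60% | 1.40 | 1.31 | 1.27 | 1.25 |

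3. Say whether 40% is the unexposed or the overall incidence, and use that meaning in both sections. If it is the overall rate, restate the power (66% at an even split); if it is the unexposed rate, restate the expected number of cases.
4. As a minor addition, keep twelve variables as the maximum but apply the ratio of about ten cases per variable, implied by 122/12, to the observed number of cases. Fewer variables then enter if cases fall below about 120.

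The cost is wording and one table. The stated power becomes less favourable for uncommon factors. Recruitment and follow-up do not change.

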### Statistical methods

We use SAS v9.3 software (SAS institute, Cary, NC, USA) for data analysis, and will not impute missing data. A significance level of 5% will be considered for the analysis.

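### At the plan's own 30% loss, a cohort of 400 leaves 280 analysable patients, not the 305 on which the 80% power and the expected event count are based

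*Protocol article*

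**What the plan says.** The Sample size section starts from the cohort's main objective, finding factors associated with PTSD at 3 months. Its premise is "Considering the hypothesis of a 40% incidence of PTSD in the" unexposed group, and it states that "the inclusion of 305 patients should allow", "with an alpha risk of 0.05, and a power of 80"%, the investigators "to identify factors associated with a relative risk of at least 1.4". It then gives the reason for the larger draw, "As we anticipate 30% of the subjects may be either lost to follow-up or unwilling to participate at 3 months", and concludes that "we will randomly select a cohort of 400 patients". The section on constitution of the cohort repeats 400.

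The section on primary outcome criteria analysis shows that 305 is meant as the number left after loss: "Among 305 analyzable patients, with a 40% incidence rate of PTSD, we expect 122 patients in the PTSD group". Directly after this it limits the multivariable model to twelve explanatory variables. The Statistical methods section says that the investigators "will not impute missing data". No replacement of patients who are lost or decline is described.

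**The concern.** The three figures 305, 30% and 400 stand within two consecutive paragraphs and are linked by the plan's own reasoning, yet 400 less 30% is not 305. The 30% already covers both lost and unwilling patients. With neither imputation nor replacement, those patients are simply absent from the analysis of the cohort's primary endpoint. The stated 80% power and the expected event count therefore both rest on a number that the plan's own loss figure does not deliver. Missing covariates in the multivariable model could only reduce the analysed number further.

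**Working it through.** **Inputs.** From the Sample size section: alpha 0.05, power 80%, p1 = 0.40 in the unexposed, relative risk 1.4 so p2 = 0.40 × 1.4 = 0.56, N = 305, loss 30%, cohort 400. From the primary outcome criteria analysis: 305 analysable, 40%, 122 events, at most twelve variables. Assumed, because not stated: a two-sided test and a 1:1 split of exposed to unexposed.

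**Step 1. Reproduce 305.** Two-proportion test with pooled variance, p̄ = 0.48:

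n per group = [1.960 × √(2 × 0.48 × 0.52) + 0.842 × √(0.40 × 0.60 + 0.56 × 0.44)]² / 0.16² = (1.385 + 0.587)² / 0.0256 ≈ 151.9, so 152 per group and 304 in total.

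This matches 305 to within one patient and supports both assumptions. A one-sided test would give 240, and a two-sided test with continuity correction 330.

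**Step 2. Apply the 30% loss.**
- Left from 400: 400 × 0.70 = 280, which is 25 short of 305.
- Needed to keep 305: 305 / 0.70 = 435.7, so 436.
- Largest loss that 400 can absorb: 1 − 305/400 = 23.75%.

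**Step 3. Power at the number delivered (1:1).** Power = Φ{(0.16 × √n − 1.385) / 0.697}, with n per group.
- N = 305 (n = 152.5): Φ(0.847) = 80.2%.
- N = 280 (n = 140): Φ(0.729) = 76.7%. Exact enumeration of the chi-squared test gives 76.3%.
- Relative risk detectable with 80% power at N = 280: 1.417, against 1.40 at N = 305.

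**Step 4. Range over the unstated split.** Same test, with p̄ weighted by group size:

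| Exposed : unexposed | N = 305 | N = 280 |
|---|---|---|
| 1:1 | 80.2% | 76.7% |
| 1:2 | 75.5% | 71.9% |
| 2:1 | 75.4% | 71.7% |
| 3:1 | 68.1% | 64.3% |
| 1:4 | 61.7% | 58.0% |

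**Step 5. Expected events at 280.** The two sections use 40% differently, so there are two answers.
- 40% as the overall incidence (primary outcome criteria analysis): 305 × 0.40 = 122 becomes 280 × 0.40 = 112. With twelve variables that is 112/12 = 9.3 events each, against 122/12 = 10.2.
- 40% in the unexposed only (Sample size), relative risk 1.4, 1:1: overall incidence (0.40 + 0.56)/2 = 0.48, so 280 × 0.48 = 134 events, or 134/12 = 11.2 each.

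The two bases cannot be mixed. If overall incidence is 40% at 1:1 with relative risk 1.4, the groups have about 33% and 47%, and power at 280 is Φ{(0.1333 × √140 − 1.358) / 0.686} = Φ(0.320), about 63%. So 77% power belongs with about 134 events, not with 112.

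**The case against.** Several defences of the plan's figures can be tried. The 305 might be a number before loss, but the analysis section calls it analysable. The reminders and repeat contact attempts might hold loss below 30%, but the plan attaches no lower figure to them. So 400 does not stand.

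The stronger objection is about size. The gap is 25 patients, about 3.5 points of power (80.2% to 76.7%), and a detectable relative risk of 1.42 instead of 1.40. This is an observational study of predictors. Neither the endpoint, the method of analysis nor the validity of the estimates is affected. That objection holds, and it limits the severity.

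A reader might also infer more than the document supports:
- **That the 122 events are missed and only eleven variables are allowed.** This takes 40% as the overall incidence. On the Sample size section's basis, 280 patients give about 134 events, more than 122. A rule of ten events per variable is not stated either; it is inferred from 122 and twelve.
- **That 400 came from multiplying 305 by 1.30 (396.5) instead of dividing by 0.70.** This is plausible, but the document does not say so, and the shortfall does not depend on it.
- **That 36 more patients are readily available from about 1500 already enrolled.** The 1500 is a projection. The Objectives and Methods/design sections draw the cohort only from patients at moderate or high risk, while the section on constitution of the cohort also lists a stratum with IES-R below 12. The pool may be well below 1500.

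**Conclusion.** The sample-size statement contradicts itself and should be corrected; severity is moderate. That 400 selected at 30% loss gives 280 analysable patients, and that 436 would be needed for 305, follows from the plan's figures without any assumption. The power of about 77% for a relative risk of 1.4 (80% for about 1.42) rests on a two-sided test and a 1:1 exposure split, neither stated but together reproducing 305. Among the splits examined, every unequal one gives lower power, down to 58% at 1:4. That the event count needs recomputing is certain. Whether it falls to 112 or is about 134 depends on which meaning of 40% the plan adopts, so the documents do not establish that twelve variables are too many.

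**What to change.** 1. In the Sample size section, either restate the result for 400 selected (280 analysable at 30% loss, about 77% power for a relative risk of 1.4, or 80% for 1.42, two-sided, under a declared 1:1 split), or justify an expected loss of at most 23.75% and keep 305.
2. If the figures are restated for 280, replace 305 with 280 in the primary outcome criteria analysis. In either case, compute the expected events on one declared incidence basis used in both sections. At 280, if 40% applies to the unexposed, about 134 events are expected and the limit of twelve variables stands. If 40% is the overall incidence, 112 events are expected (9.3 per variable); the limit then needs its own justification, and the power must be recomputed on that basis (about 63% at 1:1).
3. Selecting 436 is an alternative only if the step 1 patients eligible for the cohort are numerous enough.

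The first two changes cost wording only. The third adds 36 mailings and, at 30% loss, about 25 completed telephone interviews (36 × 0.70) of 15 to 30 minutes each.
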